#### 2.3.3. Exercise Capacity

Exercise capacity will be measured using the modified Balke treadmill protocol previously validated on a large population-based sample of children aged 7–18 years [28]. After 30 min of the seated rest, to familiarize participants with the treadmill speed, the first three minutes of the entire protocol will consist of walking on the flat without an incline with the speed set at 5.3 km/h. After the first three minutes, the incline of the treadmill will increase to 6%, and afterward by 2% each minute until 22%. After reaching 22%, the angle of the treadmill will be constant and, at each subsequent minute, the treadmill speed will be increased by 0.5 km/h until volitional exhaustion. 

The validated Pictorial Children’s Effort Rating Table (PCERT) will be used to measure exhaustion during exercise capacity assessments [29]. The PCERT is a visual assessment scale suitable for children to effectively self-report the perceived rate of exertion during physical activity by means of a verbal, numerical, and pictorial representation scale. The scoring is based on a scale from 1 to 10, where 1 is “very, very easy” and 10 is “so hard I’m going to stop” [30]. Participants will be asked to rate their perceived exertion during the treadmill test with use of the PCERT: before the test, at the 5th minute of the test, and immediately at the end of test. Standardized verbal encouragement will be given throughout the test. Heart rate (HR) will be monitored continuously during the test using the POLARV800 (Polar Electro OY Finland). Breathing parameters will be measured by the “breath-to-breath” method using the Cortex MetaMax 3B ergospirometer system (Biophysik GmbH, Leipzig, Germany). The gas analyses will be sampled at 15 s intervals. It is expected that most participants will not achieve maximal oxygen uptake (VO_2_max) values as described by a plateau in uptake of oxygen, respiratory exchange ratio (RER) > 1.5, HR 220—age or rating in PCERT scale 9 or 10. The peak oxygen uptake values will be established from the highest-achieved-intensity 15 s samples. The treadmill test will be terminated for safety using the following criteria: HR > 200 bpm, RER > 1.1, dyspnea or neurological symptoms.

It is planned to calculate Oxygen-Uptake Efficiency Slope (OUES) from the collected data. The OUES utilizes data from the entire duration of a graded exercise test; however, it is not necessarily dependent on achieving a maximal exercise response as is required when VO_2_max is assessed [31,32]. OUES is unbiased by maximal effort, test duration, or engagement of the patient, which can be challenging in a population of children. The OUES represents how effectively the oxygen is extracted by the lungs and used in the periphery and is derived from the logarithmic relation between oxygen uptake and minute ventilation [33]. OUES values, absolute or indexed to weight, height, age, body surface area, or percentage of predicted, can be used. Body surface area will be calculated using the equation of Haycock et al. [34], validated for children.

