### 2.1. Study Population

Participants will be recruited from Warsaw’s primary schools and primary health-care units according to the inclusion criteria: (i) symptoms of post-COVID-19 condition lasting more than one month following initial COVID-19 infection confirmed by the diagnosis by general practitioner (including obligatory fatigue and shortness of breath/respiratory problems); (ii) age 10–12 years old. As it has been suggested that a positive COVID-19 test is not required for a diagnosis of post-COVID-19 condition [27], there will be an optional inclusion criteria: positive RT-PCR test and/or positive result in test for antibodies against the SARS-CoV-2 coronavirus 1–8 months prior to the study start. The exclusion criteria will consist of: absolute contraindications to exercise; unstable cardiac conditions; currently engaged in regular exercise training more than twice per week. The necessary minimum total number of participants (n = 84) was obtained using the G*Power program assuming detection of a moderate effect size of REPETITIONxGROUP interaction (d = 0.50 or eta square 0.06) for exercise capacity and fatigue with a significance level of 0.05 and statistical power of 0.85.

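### Two of the four listed signs of VO2max cannot be met under the protocol's own treadmill safety stops, and peak VO2 is capped by rule in any child who reaches a stop before exhaustion

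*Protocol article*

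**What the plan says.** Section 2.3.3 of the protocol article describes a graded treadmill test. Once the steepest incline is reached, the load keeps rising: "the treadmill speed will be increased by 0.5 km/h until volitional exhaustion". The section then says what would count as a maximal result and does not expect many children to get there: "It is expected that most participants will not achieve maximal oxygen uptake (VO_2_max) values". The signs it lists are a "plateau in uptake of oxygen, respiratory exchange ratio (RER) > 1.5, HR 220—age or rating in PCERT scale 9 or 10". Peak uptake is defined by the highest intensity reached: "The peak oxygen uptake values will be established from the highest-achieved-intensity 15 s samples". The paragraph closes with the stop rule: "The treadmill test will be terminated for safety using the following criteria: HR > 200 bpm, RER > 1.1, dyspnea or neurological symptoms".

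Section 2.1 limits entry to children aged 10 to 12. The end of Section 2.3.3 also plans OUES from the same test. It describes OUES as not dependent on a maximal response and not biased by test duration. The Objectives place exercise capacity in the primary aim, but the article does not name peak VO2, OUES or any other single variable as the exercise-capacity outcome.

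**The concern.** The signs of maximal effort and the safety stops stand in the same paragraph, and for heart rate and RER the stop comes first. A reader of the results could take a missing heart-rate or RER sign as a finding about the children, when the stop rule alone makes it impossible.

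The second issue is what the recorded peak VO2 means. In one child it is the uptake at exhaustion. In another it is the uptake when heart rate passed 200 bpm or RER passed 1.1, or when dyspnea or neurological symptoms ended the test. These are different quantities under one name. A child stopped by a limit at both visits is compared at that limit, so any gain beyond it is not seen. Exercise capacity belongs to the primary aim and to the sample-size statement in Section 2.1, so the choice of variable bears on the main conclusion.

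**Working it through.** **Inputs, all from the protocol article.** Age 10 to 12 (Section 2.1). From Section 2.3.3: heart-rate sign 220 minus age; RER sign above 1.5; heart-rate stop above 200 bpm; RER stop above 1.1. The plan gives no derived figure to reproduce here; the check sets its thresholds against each other.

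**Step 1, heart rate.** Gap = (220 − age) − 200.
- Age 10: 220 − 10 = 210; gap 10 bpm; 200/210 = 95.2%.
- Age 11: 220 − 11 = 209; gap 9 bpm; 200/209 = 95.7%.
- Age 12: 220 − 12 = 208; gap 8 bpm; 200/208 = 96.2%.

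At every eligible age the test is ended before the sign is reached.

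**Step 2, RER.** 1.5 − 1.1 = 0.4. The test is ended before this sign is reached as well.

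**Step 3, the other two signs.** Neither the oxygen-uptake plateau nor a PCERT rating of 9 or 10 has a numeric stop set against it. Both remain attainable. The list is joined by the word *or*, so a child can still show a maximal effort through one of these two.

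**Step 4, effect on peak VO2.** There are two cases.
- The child stops voluntarily below both numeric limits and without a symptom stop. Peak VO2 is the uptake at exhaustion, and the rule has no effect.
- The child meets a stop criterion first. Peak VO2 is the uptake at that point. The stop limits heart rate or RER and not VO2 itself, so a gain can still appear as more oxygen taken up at the same limit. The part of a gain that lies beyond the limit is lost.

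**Step 5, how many children.** The documents give no figure. As an illustration only, assume that the heart rate a child would reach at exhaustion is normally distributed with SD 10 bpm. The share passing 200 bpm is then 1 − Φ((200 − mean)/10):
- mean 180: z = 2.0, about 2%
- mean 190: z = 1.0, 16%
- mean 195: z = 0.5, 31%
- mean 200: z = 0, 50%

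The means and the SD are assumptions. RER and symptom stops are not counted. The range of 2% to 50% shows that the share cannot be derived from the protocol.

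**The case against.** The best defence is that the signs of VO2max are descriptive and not instructions to the test staff. They stand in a sentence saying that most children will not reach VO2max, the outcome is called peak and not maximal uptake, and OUES is planned because tests are expected to be submaximal. A safety stop can also coexist with exhaustion as the ordinary end of a test. All of this stands. It means the test can be run as written. It does not make the heart-rate and RER signs attainable, and it does not say how a peak value from a rule-stopped test should be read.

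Three stronger readings are tempting, and the documents support none of them.
- *Every recorded peak VO2 is cut off by the stop rule.* Children who stop voluntarily below the limits are unaffected, and their share is unknown.
- *The dyspnea stop is triggered by a symptom that every child must have to enter.* The entry wording in Section 2.1 is "including obligatory fatigue and shortness of breath/respiratory problems". It allows other respiratory problems, and it describes symptoms lasting more than a month, not an event on the treadmill.
- *The primary outcome is invalid.* Peak VO2 is never named as primary, and OUES comes from the same test.

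A reader might also infer bias between arms, because the Limitations section says that blinding is not feasible and a dyspnea stop involves judgement. Heart-rate and RER stops are instrument readings and leave less room for that. If training reduces dyspnea and a child goes further, this may be a real gain. A fixed limit would more plausibly hide a gain than create one. The documents show no difference in stop reasons between arms; reporting the reasons would let readers look for one.

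**Conclusion.** Wrong as written, in a limited sense. With the stops applied as stated, two of the four listed signs of VO2max cannot be met: the heart-rate stop lies 8 to 10 bpm below its sign, and the RER stop lies 0.4 below its sign. This rests only on the article's own figures and on age in completed years.

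Peak VO2 is capped by rule in children who reach a limit before exhaustion, and only in them. The direction of concern is a hidden training gain and a mixture of end points. Its size cannot be stated from the documents, and the shares under working depend on assumed heart rates. The conclusion on exercise capacity can be protected with a measure the plan already includes, provided it is given that role.

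**What to change.** **Clinical criteria.** The clinical team must reconcile the signs of maximal effort, volitional exhaustion as the end point, and the safety stops in Section 2.3.3. This review takes no view on which figure is right.

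**Analysis.** Name OUES, in one stated form, as the main exercise-capacity variable. This relies on the protocol's own description of OUES as not dependent on a maximal response, which was not tested here. Report the other quantity as *VO2 at test end*, in a secondary role.

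**Recording.** Record the reason for stopping each test (volitional, heart rate, RER, dyspnea, neurological symptoms) and report it by arm and visit.

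**Sensitivity analysis.** Any repeat of the VO2 comparison that leaves out rule-stopped tests should be labelled as sensitivity only. For the post-intervention test it selects on an event after randomisation, so the remaining groups are no longer the randomised ones.

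**Cost.** A change of wording and one field on the test form. Peak VO2 could no longer serve as the main exercise-capacity measure.

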#### 2.3.4. Fatigue

Fatigue will be measured using the Polish adaptation of the Cumulative Fatigue Symptoms Questionnaire (CFSQ) validated by Kulik and Szewczyk [35]. This questionnaire measures the level of chronic fatigue and severity of individual symptoms including general fatigue, decreased vitality, mental overload, somatic symptoms, anxiety, and discouragement. It includes 30 statements with responses of “never”, “sometimes”, and “often”, where the responses are assigned the values of 0, 1, and 2, respectively. The response scores are added together and the CFSQ total score ranges from 0 to 60; the higher the score, the greater the severity of the symptoms of chronic fatigue [35]. Scores are categorized as low (0–14), average (15–30), high (31–45), and very high (46–60). The more detailed characteristics of fatigue will be explored by adding up the scores in the subscales: general fatigue, weakened vitality, psychological overload, somatic symptoms, anxiety, and discouragement about studying and school.

#### 2.3.5. Health-Related Quality of Life

Health-related quality of life (HRQOL) will be measured with the Polish version of the Pediatric Quality of Life Inventory 4.0 Generic Core Scales (PedsQL^TM^ 4.0) for children and for parents. The Polish version of PedsQL^TM^ 4.0 was validated by Talarska et al. [36]. PedsQL^TM^ 4.0 is a brief, standardized, generic assessment instrument that systematically assesses perception of HRQOL in healthy children and those with acute and chronic health conditions. It is based on a modular approach to measuring HRQOL. The questionnaire contains 23 questions divided into the following subsections: physical functioning (8 items), emotional functioning (5 items), social functioning (5 items), and school functioning (5 items). The sum of these areas is the overall quality of life (total score). The responses are reported on a 5-point Likert scale ranging from 0 (no problem) to 4 (almost always), with a total score ranging from 0 (best HRQOL) to 100 (worst HRQOL) [37]. Further, two summarized functional children’s areas will be reported: the Physical Health Summary Score covering the area of Physical Functioning, and the Psychosocial Health Summary Score will be taken into account for analysis. Both participants and their parents will complete the questionnaire separately. It is planned to compare children’s and parents’ perception of the HRQOL of the child with post-COVID-19 condition. 

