### Objectives

The primary aim of this research project is to determine the effectiveness of land-based and water-based exercise interventions on exercise capacity and fatigue in children with post-COVID-19 condition.

The secondary aims are to determine the effectiveness of land-based and water-based exercise on health-related quality of life and pulmonary function in children with post-COVID-19 condition, and to compare outcomes to norms for healthy children.

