### 2.6. Statistical Analysis

Normality of the distributions of the quantitative variables under study will be tested using the Shapiro–Wilk test. Data will be presented as mean ± SD where appropriate. The mixed-design ANOVA will be used to compare means. The interaction of fixed and repeated factors will be analyzed. Tukey’s post hoc test will be used for detailed comparisons. For variables that do not meet the criteria of normality of distribution, data will be presented as medians and quartile range. The Mann–Whitney U test will be used to compare the groups. The variables as well as their increments will be analyzed. Effect sizes will be assessed by partial eta squared (ANOVA) or the Glass rank-biserial correlation coefficient (the Mann–Whitney U test). The agreement of children’s and parents’ responses in the PedsQLTM 4.0 questionnaire will be analyzed with the compatibility factor Kappa-k. All statistical calculations will be conducted using the Statistica 14.0.0.15 program (TIBCO Software Inc., Palo Alto, CA, USA, 2020).

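### Section 2.3.5 is inconsistent on PedsQL scoring: 23 items coded 0–4 and summed give 0–92, not the stated 0–100, and the possible repairs are not all equivalent

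*Protocol article*

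**What the plan says.** Section 2.3.5 (Health-Related Quality of Life) gives four pieces of the scoring rule:

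- Items: "The questionnaire contains 23 questions divided into the following subsections: physical functioning (8 items), emotional functioning (5 items), social functioning (5 items), and school functioning", the last area also having 5 items.
- Coding: "The responses are reported on a 5-point Likert scale ranging from 0 (no problem) to 4 (almost always").
- Aggregation: "The sum of these areas is the overall quality of life (total score").
- Range and direction: "with a total score ranging from 0 (best HRQOL) to 100 (worst HRQOL"), with a literature reference.

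The section also plans a Physical and a Psychosocial summary score, but gives neither a formula nor a range for them. It mentions no averaging or rescaling.

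Two other places use these scores. The Objectives name health-related quality of life in the secondary aims, which end with the intention "to compare outcomes to norms for healthy children". Section 2.6 says that the agreement between children's and parents' PedsQL responses "will be analyzed with the compatibility factor Kappa-k"; no weighting is mentioned.

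**The concern.** Item count, coding, aggregation and range are all stated in one paragraph, so a reader can check them against each other, and they do not agree. This is a stated rule that fails to yield its stated scale. It is not simply a detail left out of a condensed article.

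Two things are at stake. First, anyone who scores the questionnaire must choose how to get from 0–4 items to a 0–100 total. Some choices differ in how much weight physical functioning receives, and in an exercise trial that is a plausible area of change. If the choice is open when the data are seen, it is an avoidable degree of freedom. Second, a comparison with norms needs both sets of scores on the same scale and in the same direction.

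The agreement analysis is a smaller, related matter. The responses have five ordered levels, and an unweighted kappa ignores the order.

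**Working it through.** **Inputs** (all from section 2.3.5 unless noted): areas of 8, 5, 5 and 5 items; item codes 0–4; areas summed; stated total 0–100. For comparison, section 2.3.4 has 30 CFSQ items coded 0–2 and summed.

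**1. Does the stated range follow from the stated rule?**

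- Items: 8 + 5 + 5 + 5 = 23, as stated.
- Maximum raw sum: 8×4 + 5×4 + 5×4 + 5×4 = 32 + 20 + 20 + 20 = **92**, not 100.
- A raw sum of 100 would need 100/4 = 25 items.
- If each area is first put on 0–100 and the four are summed, the maximum is 4 × 100 = **400**.
- With items coded 1–5 instead, the sum would run from 23 to 115.

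No summing rule tried gives 0–100. The same check on the CFSQ does work: 30 × 2 = 60, matching "The response scores are added together and the CFSQ total score ranges from 0 to 60".

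**2. Which rules do give 0–100?**

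- A: mean of 23 items × 25, with maximum 4 × 25 = 100.
- B: raw sum × 100/92, with maximum 92 × 1.087 = 100. With all items answered, A and B are the same score, since 25/23 = 100/92.
- C: mean of four area scores, each rescaled to 0–100, with maximum 100.

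**3. Are they equivalent?** A and B are a constant multiple of the raw sum, but C is not.

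| | Weight of physical functioning | Change in total if every physical item moves one level |
|---|---|---|
| A or B | 8/23 = 35% | 8 × 25/23 = 8.7 points |
| C | 1/4 = 25% | 25/4 = 6.25 points |

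The ratio is 6.25/8.7 = 0.72, so in this example the movement is 28% smaller under C.

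**4. Effect on the planned tests.** Going from the raw sum to A or B multiplies every total by 1.087. With all items answered, the ANOVA F tests, p-values and partial eta squared do not change, nor do the Mann–Whitney test and the rank-biserial coefficient. Going from A to C reweights the areas, so these results can change.

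**5. Effect on norms, conditionally.** If raw sums were set against norms on 0–100, each total would be 92/100 = 0.92 of its proper value, that is 8% too low. The scale midpoint would be 46 instead of 50.

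**6. Kappa on five levels.** Disagreement weights for two possible child–parent pairs:

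| | 0 versus 1 | 0 versus 4 |
|---|---|---|
| Unweighted | 1 | 1 |
| Quadratic, (difference/4)² | 1/16 = 0.06 | 1 |

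Unweighted kappa counts a one-level difference as fully as a four-level one.

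**The case against.** The strongest reply is that this is loose wording about a standardized instrument. The range sentence carries a reference, an article commonly leaves the scoring transformation to such a source, and summing areas may only mean forming a composite. The only scale that the article states for the total is 0–100, and a simple linear rescaling reaches it. The outcome is secondary, and a constant factor does not alter the group comparisons.

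Much of this stands. It removes several stronger readings that a reader might infer:

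- *That the scale is arithmetically impossible.* It is unreachable by the rule as written, but rules A, B and C all reach it.
- *That totals and norm comparisons will be on the wrong scale.* The article does not say that raw sums will be analysed or read as 0–100. It gives no PedsQL norm; the only norm comparison set out in detail is for lung function, in section 2.3.6.
- *That a child with a skipped item automatically scores better.* This assumes that blanks count as 0. The article does not say so, and section 2.7 plans a complete-case analysis.
- *That the direction is unclear.* One direction is stated, and it agrees with the item coding.
- *That kappa is applied to a near-continuous score and will understate agreement.* Section 2.6 speaks of responses, which section 2.3.5 uses for the five-level answers. A weighted kappa is not ruled out.

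What the reply does not remove is the contradiction itself. The article specifies summing, and the section just before it uses a sum rule that works literally. Nor is every repair a constant factor, as the comparison of A with C shows.

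**Conclusion.** The point holds in a limited form. Section 2.3.5 states a sum whose maximum is 92 and a scale that ends at 100, and it omits the step that would connect them. The repairs differ in substance: physical functioning carries 35% or 25% of the total, depending on the rule.

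The 8% shortfall against norms is conditional on raw sums being compared with norms on 0–100, which the document does not state. Invariance of the between-group tests holds for a constant rescaling with all items answered, and not for a change in area weights. The 28% figure belongs to an illustration in which only the physical items move. Whether the stated direction and range match the instrument's published scoring cannot be settled from this document.

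The primary outcomes, exercise capacity and fatigue, are untouched, as is the sample size. This is a minor to moderate correction and need not hold up the trial. The weighting of kappa is a low-cost improvement in method; the article makes no demonstrated error there.

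**What to change.** In section 2.3.5, replace the statement that the areas are summed with one formula that yields 0–100 for all three scores. For example, use the mean of answered items × 25 over 23 items (total), 8 items (Physical) and 5 + 5 + 5 = 15 items (Psychosocial). This keeps the stated direction, with 0 as best. Say how the answered-items rule fits with the complete-case rule in section 2.7. If an equal-area total (rule C) is intended instead, state that explicitly.

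Before any comparison with norms, confirm that the PedsQL norms used have the same scale and direction as the trial's scores.

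In section 2.6, specify a weighted kappa (for example quadratic) for the five-level child and parent responses, and an absolute-agreement ICC for the summary and total scores.

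The cost is two or three sentences, settled before analysis, with no additional data.
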